## Abstract

**Background:**

Major depression is a common mental disorder that substantially impairs quality of life and has high societal costs. Although psychotherapies have proven to be effective antidepressant treatments, initial response rates are insufficient and the risk of relapse and recurrence is high. Improvement of treatments is badly needed. Studying the mechanisms of change in treatment might be a good investment for improving everyday mental health care. However, the mechanisms underlying therapeutic change remain largely unknown. The objective of the current study is to assess both the effectiveness of two commonly used psychotherapies for depression in terms of reduction of symptoms and prevention of relapse on short and long term, as well as identifying underlying mechanisms of change.

**Methods:**

In a randomised trial we will compare (a) Cognitive Therapy (CT) with (b) Interpersonal therapy (IPT), and (c) an 8-week waiting list condition followed by treatment of choice. One hundred eighty depressed patients (aged 18-65) will be recruited in a mental health care centre in Maastricht (the Netherlands). Eligible patients will be randomly allocated to one of the three intervention groups. The primary outcome measure of the clinical evaluation is depression severity measured by the Beck Depression Intenvory-II (BDI-II). Other outcomes include process variables such as dysfunctional beliefs, negative attributions, and interpersonal problems. All self-report outcome assessments will take place on the internet at baseline, three, seven, eight, nine, ten, eleven, twelve and twenty-four months. At 24 months a retrospective telephone interview will be administered. Furthermore, a rudimentary analysis of the cost-effectiveness will be embedded. The study has been ethically approved and registered.

**Discussion:**

By comparing CT and IPT head-to-head and by investigating multiple potential mediators and outcomes at multiple time points during and after therapy, we hope to provide new insights in the effectiveness and mechanisms of change of CT and IPT for depression, and contribute to the improvement of mental health care for adults suffering from depression.

**Trial registration:**

The study has been registered at the Netherlands Trial Register, part of the Dutch Cochrane Centre (ISRCTN67561918)

## Background

With a lifetime prevalence of 17%, depression is a major health problem with serious clinical and social consequences. It is expected that depression will be the leading global cause of years of health lost due to disease in 2030 [1]. With initial response rates up to 60%, and the majority of patients regaining their normal level of functioning within three years, certain psychotherapies and antidepressant medication have proven efficacy in treating acute Major Depressive Disorder (MDD) [2,3]. This might sound promising, but at least 40% of depressed patients do not respond to initial treatment at all. Furthermore, depression has an unfavourable prognosis; even when treated effectively in the acute phase, recovery is often incomplete, which increases the chance of relapse and recurrence up to 87% over 15 years [4-7].

With this in mind, the challenge in contemporary depression research is to improve treatments to increase acute response rates and prevent relapse and recurrence in the long term. Many researchers agree that knowledge of underlying mechanisms that can explain therapeutic change is a key to improving treatment [8,9]. Knowing how a therapy works would allow honing its components to make it more efficient and (cost-)effective [10]. The current study will focus on the effectiveness, prevention of relapse and recurrence and mechanisms of change of two commonly used types of psychotherapy for depression: Cognitive Therapy (CT) [11] and Interpersonal Therapy (IPT) [12]. A rudimentary analysis of the cost-effectiveness from a societal perspective will be embedded.

### Effectiveness

Of the psychotherapeutic interventions for depression, CT and IPT might be the two best studied and empirically validated [13-15]. They come from different theoretical backgrounds: CT derives from Beck's cognitive theory and explains depression as a result of maladaptive information-processing, whereas IPT links depressive episodes to distressing life events and insufficient social support [12,16]. Nonetheless, both therapies have proven to be well-standardized, efficacious treatments for acute treatment of MDD [3,12,17-23]. There is no consensus yet about whether the effect of one therapy outperforms the other. Many studies have investigated the effects of CT and IPT separately, but only 2 large studies have compared them head-to-head [24-26]. However, doubts have arisen about the validity of one of these studies because analysis of treatment adherence showed no contrast between the two intervention groups [24,27]. Thus, the current view is based on only one methodologically well-designed study. Therefore, there is a need for renewed head-to-head comparisons of both therapies.

### Relapse Prevention

In addition to the fact that CT and IPT have shown to be efficacious acute treatments of MDD, they may also reduce the risk of relapse (episode of MDD after remission) and recurrence (episode of MDD after recovery) in the long term. The effects and evidence differ for the two therapies. Research has shown that CT has an enduring effect that extends beyond the end of therapy [12,28-33], thereby reducing the chances of relapse and recurrence. The evidence for this is strong and consistent [31,34,35]. However, the long term effect of IPT has not been tested extensively yet. Up until now it has only been tested as a maintenance treatment [36,37], and the question remains whether IPT also has an enduring effect that remains after therapy is finished. This question should be further explored. Insight in the long term effects of IPT furthermore creates the opportunity to compare CT and IPT to assess whether one therapy is superior to the other in preventing relapse and recurrence in the long term [15].

### Mechanisms of Change

As noted above, insight into mechanisms of change might contribute to the process of therapy improvement. However, the mechanisms that cause therapeutic change are still largely unknown. Despite several research attempts to identify the mechanisms of change in psychotherapy, no study has identified a model that explains change in CT or IPT completely [38,39]. Mechanism research has to cope with several methodological and theoretical difficulties [40,41]. Theoretical difficulties arise because there are conflicting hypotheses on the mechanisms and there is no consensus about the most important causes of change [38,42]. For example, it is unclear whether therapeutic change can be better explained by change in treatment specific factors [42-45] or non-specific (common) factors [46-48]. Specific factors are elements marked as the active causes of change in the theory of the therapy, such as change in cognitions in CT and optimization of interpersonal functioning in IPT. Non-specific factors refer to elements in a therapy that contribute to improvement, but that are common to all psychotherapies, such as expectancy and therapeutic alliance [49]. Furthermore, it is not exactly known whether changes achieved in therapy are best reflected by explicit or by implicit measures of psychopathology. Explicit measures depend on introspection, and a disadvantage is that it is known that people do not have access to all of the mechanisms that underlie their behaviour [50]. An implicit measure is defined by De Houwer, Teige-Mocigemba, Spruyt, and Moors (2009) as "a measurement outcome that is causally produced by the to-be-measured attribute in the absence of certain goals, awareness, substantial cognitive resources, or substantial time" (p. 350) [51]. To the extent that implicit measures reflect uncontrollable, unaware, fast mechanisms, they could provide information that augments that from explicit measures [52].

Furthermore, methodological difficulties arise because many study designs do not meet the criteria for reputable mechanisms research [40,41]. Theories often explain change in terms of causal processes. However, in many studies it is difficult to identify temporal relationships in order to investigate these causal pathways because of the absence of an appropriate time line and assessment on multiple time points [40,41]. It is clear that there is a need for renewed, methodologically well-considered mechanism research.

The question remains what is necessary for proper mechanism research. According to Kazdin (2007), a first step into investigating mechanisms of change is studying mediating variables [40]. A mediator explains why and in what way a treatment has an effect on the outcome, and plays a crucial role in the development of causal pathways. In identifying mediators, Kazdin has built upon the MacArthur guidelines of Kraemer et al. (2001) [53] which are based on the more traditional guidelines for statistical mediation formulated by Baron and Kenny (1986) [54]. In addition to statistical mediation and association, Kazdin emphasizes the importance of the temporal relationship, and consistency and specificity of the mediator. The importance of the aspect of temporality is also emphasized by Murphy et al (2009) [55]. Taking this into account, the current study will investigate potential mediators of CT for depression and test their specificity in comparison to IPT, and vice versa, by measuring multiple potential mediators and outcomes at multiple time points during and after therapy. This method enables us to investigate temporal relationships between changes in potential mediators and symptom reduction and to assess whether change in a mediator precedes, follows from, or goes together with changes in depression. In addition, this method can show us whether change in one mediator precedes change in another mediator.

### Main research questions and Hypotheses

The following main research questions were formulated:

• Are CT and IPT effective interventions in treating the acute phase of MDD and is one therapy superior to the other?

• What are the underlying psychological mechanisms of change in CT and IPT and are these mechanisms therapy-specific?

• Are CT and IPT effective in preventing relapse or recurrence of MDD in the long-term? Is one therapy superior to the other, and if so, how can these preventive effects be explained?

In line with previous research, it is hypothesized that the amount of change in depressive symptoms after therapy will be similar in both the CT and the IPT group, indicating that both treatments are just as effective in treating depression in the acute phase [14,24,56,57]. Because both therapies originally stem from different theoretical backgrounds, we expect that both treatments target depression through different key processes. It is expected that changes in cognitive schemas, attitudes, and cognitions are the most significant contributors to symptom change in CT, whereas in IPT it is assumed that improvement of interpersonal functioning will lead to a reduction of symptoms [12,16]. With regard to the mechanisms of change, many hypotheses are possible, especially when it comes to the order of change and causal pathways that lead to recovery. Following the theories one would expect that change in cognitions (CT) and interpersonal functioning (IPT) precede symptom change. Furthermore, we expect that it is the direct comparison of explicit versus implicit measures that will elicit new insights into the underlying mechanisms of change. To the extent that implicit measures reflect uncontrollable, unaware and fast mechanisms, they can provide useful additional information as compared to explicit measures. As to the prevention of relapse, we hypothesize that both CT and IPT may reduce the risk of relapse and recurrence in the long term. However, we expect CT to prevent relapse to a greater extent, because it has shown to have an enduring effect that extends beyond the end of therapy, while IPT so far only seems to be effective in treating depression as long as the treatment is continued [58].

## Methods

### Design of the study

We will conduct a randomised controlled trial (RCT) in which participants will be allocated to one of three conditions: (a) CT (*N *= 75), (b) IPT (*N *= 75), (c) or a waiting list condition followed by treatment of choice (*N *= 30). Participants allocated to the waiting list condition start their treatment after an 8-week waiting period. To compensate for the waiting, they may choose their preferred treatment (CT or IPT). The anticipated flow of subject enrolment is graphically shown in Figure 1. The Medical Ethics Committee of Maastricht University approved the study protocol. The study is registered at the Netherlands Trial Register, part of the Dutch Cochrane Centre (ISRCTN67561918).

**Figure 1 F1:**
[figure not shown]
**Flow of the Participants**.

### Participants

The population we aim to investigate consists of 180 depressed adults. Patients will be eligible to participate if they meet the following criteria: age between 18 - 65 years old; the presence of a depressive episode as indicated by a diagnosis on the Structural Clinical Interview for DSM-IV Axis I disorders (SCID-I) [59]; internet access and an e-mail address; sufficient knowledge of the Dutch language; no chronic depression (>5 years); no current use of antidepressant mediation; no severe psychiatric co-morbidity, drugs- and alcohol abuse/dependence and oligophrenia.

### Sample size

To calculate the sample size of the CT and IPT group, we combined rudimentary findings from previous randomised trials, which resulted in a mean relapse/recurrence rate of 33% after two years of follow-up, compared to 67% following antidepressant medication and/or clinical management [28,29,31-33]. Based on these results, we assume a difference of 20% in relapse between CT and IPT. Using survival analysis (two-sided, α = 0.05, power = 80%), we calculated that 75 patients per treatment condition would suffice to detect this statistically significant difference rate in relapse/recurrence between the two conditions in the long term.

A waiting list condition is included to investigate whether the effects of CT and IPT exceed the outcome in patients who do not receive treatment, a finding that has been demonstrated in numerous previous studies [60-63]. A power calculation showed that 30 participants in the waiting list condition will be sufficient to detect a statistically significant difference between the two active conditions combined (CT and IPT) and the waiting list after eight weeks.

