### Randomisation and procedure

Eligible participants will be contacted by telephone for a baseline visit at the university. Preceding this initial visit to the research centre, participants will receive an appointment letter, including study information. This will allow them to consider their study participation well before they agree to participate (approximately one week). Furthermore, to decrease the burden of the first assessment, participants will be asked to already fill out a substantial part of the baseline questionnaires at home. Randomisation will take place after informed consent is obtained and the second part of the baseline questionnaires are filled out. In our design we prestratified groups by first (1 episode) and recurrent (> 1 episodes) depression. The researcher will press the 'assign' button on the computer screen, after which the database randomly allocates the participant to one of the treatment conditions (CT or IPT), or to the waiting list condition by using block randomisation. This waiting list condition is included because it has been frequently argued in psychotherapy research that the effect in treatment studies cannot be attributed to the intervention(s) that are studied, unless a placebo or no-treatment group is included [65]. With regard to the nature of the treatments, blinding of the participants and researchers is not possible.

In reporting the follow-up period of the CT and IPT condition in this study, we distinguish three phases; (a) the Treatment phase (baseline to 7 months); the period when therapy will be delivered; (b) The Trial follow-up phase (month 8-12) in which depression severity will be measured monthly; and (c) The Long-term follow-up phase (12 to 24 months); the period covered by retrospective assessment. All questionnaires will be administered on a computer. Pre- and post treatment assessment (baseline and 7 months) will take place at the University. All other follow-up self-report assessments will take place at home via the internet at three, eight, nine, ten, eleven, twelve and twenty-four months after inclusion.

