### Analyses

Data-analysis will include intention-to-treat analyses, per-protocol analyses, change analyses and prognostic analyses. Analyses will include elementary head-to-head comparisons of the intervention groups as well as more complicated multivariate analyses (e.g., individual time series analysis, logistic regression analysis, multilevel analyses). Furthermore, in ancillary analysis, subgroups of the study sample according to symptom severity and DSM-IV classification will be examined for differential effects. In addition, we will determine the proportion of patients that show reliable and clinically significant improvement on the outcome measures. Our calculations will be based on the method of Jacobson and Truax [130] which prescribes that Clinical Improvement (CI) is based on both Reliable Change (RC), the extent to which the pre-to-post-difference score is reliable; and on Clinical Significant change (CSC), the extent to which post-treatment scores are clinically meaningful [131]. We will use chi-square tests to test the frequency differences in the RC, CSC, and CI between the three intervention groups.

Relapse (episode of MDD after remission) and recurrence (episode of MDD after recovery) in the course of follow-up (12 and 24 months) will be assessed using survival analysis (Cox proportional hazards regression). Furthermore, using multi-level mediation models, we will investigate various potential treatment mediators (psychological processes responsible for therapeutic change) to identify mechanisms of change. We will use the revised and expanded McArthur guidelines with a central focus on the temporal aspect [40,41]. Furthermore, we will use structural equation modelling to test the relative strength of the factors involved (path analysis), an approach already successfully applied by Oei and colleagues [48].

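### The sample size borrows two-year relapse rates without giving their time origin; if they run from end of treatment, the trial's 17 to 20 months at risk do not support the stated 80% power

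*Protocol article*

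**What the plan says.** The Sample size section pools earlier trials, which "resulted in a mean relapse/recurrence rate of 33% after two years of follow-up, compared to 67% following antidepressant medication and/or clinical management". It continues: "Based on these results, we assume a difference of 20% in relapse between CT and IPT". The settings are "Using survival analysis (two-sided, α = 0.05, power = 80"%), and the result is that "75 patients per treatment condition would suffice to detect this statistically significant difference rate in relapse/recurrence" between the conditions in the long term. The section gives no start for the two years, no month for the long-term comparison, and no separate rate for CT and for IPT.

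The trial's own clock is in Randomisation and procedure. The first phase is "the Treatment phase (baseline to 7 months); the period when therapy will be delivered". The home assessments are "at three, eight, nine, ten, eleven, twelve and twenty-four months after inclusion", so month 24 is counted from entry.

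Under Participants, every patient enters in a current depressive episode. Under Analyses, relapse is an episode after remission and recurrence an episode after recovery; both, "in the course of follow-up (12 and 24 months) will be assessed using survival analysis (Cox proportional hazards regression").

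**The concern.** In a survival comparison the number of events carries the information, so a borrowed event rate must belong to the same length of risk as the planned observation. Here the borrowed rate is tied to two years, while the trial's two years include the months in which patients are still being treated for the episode they entered with. Nobody can relapse at month 0. From the end of the treatment phase, 24 − 7 = 17 months remain. If remission is typically reached around month 4 (an assumption), the window is about 20 months.

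The sources may well have counted from the end of treatment. The five references behind the 33% all lie within the set that the Relapse Prevention section cites for this statement: "Research has shown that CT has an enduring effect that extends beyond the end of therapy". The hypotheses also rest the expected CT advantage on what happens once therapy stops. If that is the origin, the calculation assumes more exposure than the trial observes, and a non-significant Cox result would be read against a power that the design does not have.

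**Working it through.** **Inputs from the protocol article.** 33% at two years; 20-point difference; two-sided α = 0.05; power 80%; 75 per arm; treatment phase months 0–7; last assessment at month 24 from inclusion.

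**Assumptions.** Source rates are 24-month post-treatment rates; constant hazard in each arm; all 75 per arm at risk; no dropout. The second arm's rate is not stated. Three pairs 20 points apart are tried: 33% vs 53% (33% read as CT, since CT is expected to do better), 13% vs 33%, and 47% vs 67%.

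**Formulas.**
- Hazard ratio: HR = ln(1 − p1) / ln(1 − p2).
- Events required: Schoenfeld 4(1.96 + 0.842)² / (ln HR)²; Freedman (1.96 + 0.842)² × [(1 + HR)/(1 − HR)]².
- Patients per arm: events divided by (p1 + p2).
- Power with E events: Schoenfeld Φ(√E × |ln HR|/2 − 1.96); Freedman Φ(√E × (1 − HR)/(1 + HR) − 1.96).
- Rescaling to m months: p(m) = 1 − (1 − p(24))^(m/24).

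**Step 1: the plan's own figure over a full 24 months.** For 33% vs 53%, HR = 0.4005/0.7550 = 0.530. Schoenfeld needs 79 events, 79/0.86 → 92 per arm; Freedman needs 84 events, 84/0.86 → 98 per arm. At 75 per arm, E = 75 × 0.86 = 64.5 and power is 72.1% (Schoenfeld) or 69.3% (Freedman). The stated 75 does not reproduce on this reading. It is approached with a one-sided 0.05 test (73 or 77), which contradicts the stated two-sided test, or with 13% vs 33% two-sided by Freedman (74).

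**Step 2: the same hazards over 17 months.** For 33% vs 53%:
- p1 = 1 − 0.67^(17/24) = 0.247 and p2 = 1 − 0.47^(17/24) = 0.414, a difference of 16.7 points.
- E = 75 × (0.247 + 0.414) = 49.6, which is 23% fewer than 64.5.
- Schoenfeld power = Φ(√49.6 × 0.634/2 − 1.96) = Φ(0.273) = 60.7%; Freedman 58.0%.

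**Step 3: all pairs at 75 per arm** (power range is Freedman to Schoenfeld).

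| Rates at 24 months | Window | Difference (points) | Events | Power |
|---|---|---|---|---|
| 33% vs 53% | 24 | 20.0 | 64.5 | 69–72% |
| 33% vs 53% | 20 | 18.3 | 56.3 | 63–66% |
| 33% vs 53% | 17 | 16.7 | 49.6 | 58–61% |
| 13% vs 33% | 24 | 20.0 | 34.5 | 81–87% |
| 13% vs 33% | 20 | 17.4 | 29.5 | 75–82% |
| 13% vs 33% | 17 | 15.3 | 25.6 | 69–76% |
| 47% vs 67% | 24 | 20.0 | 85.5 | 71–73% |
| 47% vs 67% | 17 | 18.2 | 68.0 | 61–63% |

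**Step 4: sensitivity to hazard shape.** If relapses cluster early (Weibull shape 0.5, 33% vs 53%), the 17-month difference is 18.4 points, with 56.7 events and power of 64–67%. The loss is smaller, but power stays below 80%.

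**The case against.** The strongest reply is that the mismatch is not on the page. The Sample size section never says that the source's two years start at the end of treatment, and the cited trials are not available here. The protocol's own vocabulary points the other way: Randomisation and procedure counts the treatment phase as part of the follow-up period, and both that section and Methodological Considerations use a two-year follow-up for the whole 24 months. Read so, the borrowed rate and the trial share a clock. This stands, and it is why the finding is conditional. The shared references make a post-treatment origin the likelier reading but give neither a duration nor a starting point.

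A reader might go further and infer that the 20-point difference cannot apply to this trial. The document does not support that. The sources show a 34-point gap (67% − 33%) against another comparator; the 20 points are a planning assumption tied only to the long term, and may already allow for the window.

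Nor is the window exactly 17 months. Therapy lasts 12 to 20 sessions according to progress, and risk starts at remission, which can precede month 7. With 20 months and 13% vs 33%, the power range still includes 80%.

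Finally, for 33% vs 53% and 47% vs 67% power is short of 80% before any window is applied. On those pairs the shorter exposure deepens a shortfall that already exists; it does not create it.

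**Conclusion.** The point holds as a conditional one. The protocol article fixes a power claim on rates whose time origin it does not give, while its own 24 months start at inclusion and contain 7 months of treatment. If the source rates run from the end of treatment, a 17-month window costs about 10 to 13 points of power at 75 per arm under a constant hazard, and none of the three rate pairs reaches 80%. At 20 months only 13% vs 33% can, and only by one of the two formulas. If the source rates run from inclusion, the window argument falls away, but 33% vs 53% still gives only 69–72% over the full 24 months.

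The exact loss depends on the unstated arm rates, the hazard shape and the time of remission. Treating all 75 per arm as at risk without dropout favours the plan. It would be wrong to conclude that the source rates are known to be post-treatment rates; the document makes that likely and no more.

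**What to change.** In the Sample size section, state three things: the time origin of the borrowed rates, the horizon of the CT–IPT comparison in months, and the assumed rate in each arm. If the origin is end of treatment, convert the rates to the trial's risk window and give the assumed hazard shape and start of risk. If the origin is inclusion, do not rescale, because that would discount the rates wrongly. In either case, restate expected events, detectable difference and power at 75 per arm.

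In the report, describe the month-24 result as relapse or recurrence up to 24 months after inclusion, so that it is not taken for a two-year post-treatment rate.

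The cost is a rewritten paragraph and a label. No patients or visits are added. The downside is a stated power that will probably be less favourable than 80%.

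### The 75 per arm said to give 80% power for a 20-point CT–IPT difference in relapse gives about 70% on the most natural reading of the inputs, and less if only remitters are at risk

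*Protocol article*

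**What the plan says.** The Sample size section of the protocol article takes from earlier randomised trials "a mean relapse/recurrence rate of 33% after two years of follow-up, compared to 67% following antidepressant medication and/or clinical management". From this it says "we assume a difference of 20% in relapse between CT and IPT". The test settings are "Using survival analysis (two-sided, α = 0.05, power = 80" per cent, and the conclusion is that "we calculated that 75 patients per treatment condition would suffice to detect this statistically significant difference rate in relapse/recurrence". The paragraph does not say which therapy the 33% belongs to, and it gives no rate for the other arm, no hazard ratio and no number of events.

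Other sections bear on how to read it:

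- Relapse Prevention cites nearly the same references for CT: "Research has shown that CT has an enduring effect that extends beyond the end of therapy [12,28-33". Of the other therapy it says "the long term effect of IPT has not been tested extensively yet".
- Main research questions and Hypotheses expects CT to prevent relapse better than IPT.
- Analyses defines the events: "Relapse (episode of MDD after remission) and recurrence (episode of MDD after recovery". They are to be analysed by Cox regression.
- Background puts initial response at no more than 60% and says that "at least 40% of depressed patients do not respond to initial treatment at all".

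**The concern.** The method, alpha, sidedness, power, difference and sample size are all printed, so they can be checked against each other. On the most natural reading they do not agree.

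The calculation also treats all 75 randomised patients per arm as able to have the event. Participants enter in a depressive episode, and by the article's own definitions nobody can relapse or recur before remitting or recovering. The number that carries the power is the number who reach that state, which is smaller than 75 by an amount the paragraph does not give.

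This is the only calculation shown that sizes the CT and IPT arms, and it supports one of the three main research questions: whether one therapy is better at preventing relapse. If 80% power is quoted when the results are read, a non-significant comparison will look more informative than it is.

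**Working it through.** **Inputs.** Two-sided alpha 0.05, 80% power, 1:1 allocation, 75 per arm, 33% at two years and a 20-point gap (Sample size). CT is taken as the 33% arm (the references shared with Relapse Prevention) and as the better arm (Hypotheses). The IPT rate is then derived: 33% + 20 points = 53%.

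**Hazard ratio**, assuming proportional hazards: ln(1 − 0.33)/ln(1 − 0.53) = ln 0.67/ln 0.47 = 0.530, so |ln HR| = 0.634.

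**Expected events with 75 per arm all at risk:** 75 × (0.33 + 0.53) = 64.5.

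**Power at 75 per arm**

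- Schoenfeld: Φ(√64.5 × 0.634/2 − 1.96) = Φ(2.546 − 1.96) = 72%.
- Freedman: (1 − HR)/(1 + HR) = 0.307; Φ(√64.5 × 0.307 − 1.96) = Φ(2.464 − 1.96) = 69%.
- Comparison of two proportions: 70%. Simulated log-rank test with 20,000 runs: 71%.

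**Size needed for 80% power**

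- Schoenfeld: 4 × (1.960 + 0.842)²/0.634² = 78.1 events; 78.1/0.86 = 91 per arm.
- Freedman: (1.960 + 0.842)²/0.307² = 83.4 events; 83.4/0.86 = 97 per arm.
- Two proportions: about 95 per arm.

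**Attempts to reproduce 75**

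| Reading | Result |
|---|---|
| 33% vs 53%, one-sided 0.05 | two proportions 74.7, so 75 per arm; contradicts the stated two-sided test |
| 47% vs 67%, two-sided | 71–73% power at 75 (Freedman, Schoenfeld) |
| 23% vs 43%, two-sided | 73–77% power at 75 |
| 20% vs 40%, two-sided | 75–79% power at 75; neither rate is stated |
| 13% vs 33%, two-sided | 81–87% power at 75 |

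Of the readings tried that are anchored on a stated rate, only 13% vs 33% reaches 80% with a two-sided test. It needs either IPT to be the better arm, against the Hypotheses section, or CT at 13%, against a 33% drawn from CT trials.

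**Risk set.** If 33% and 53% are rates among remitters, the same formulas apply with n equal to the number at risk per arm:

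| At-risk fraction | Per arm | Events (n × 0.86) | Power (Freedman–Schoenfeld) |
|---|---|---|---|
| 100% | 75 | 64.5 | 69–72% |
| 80% | 60 | 51.6 | 60–63% |
| 70% | 52.5 | 45.2 | 54–57% |
| 60% | 45 | 38.7 | 48–51% |

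The last row uses the Background's ceiling on response as a proxy for remission: 0.60 × 75 = 45. The 80% and 70% rows are assumptions that show the range.

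**Difference detectable with 80% power from 33%.** With 75 at risk, 22 points gives 80% by Schoenfeld and 23 points gives 80% by Freedman. With 45 at risk, 28 points gives 79% by Schoenfeld and 30 points gives 80% by Freedman.

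**The case against.** The strongest reply is that the article never states 53% and does not name CT as the 33% arm. The result depends on that anchor, and the authors call their source findings rudimentary. This is right as far as it goes: the shortfall is shown for the most natural reading, not for every reading. But the only alternative tested on a stated rate that restores 80% conflicts with the article's own hypothesis or with the origin of the 33%, so the paragraph still needs correcting.

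A reader might go further and infer that the true power is about 50%, with at most 45 patients per arm able to relapse. The documents do not establish this. It needs three things they leave open:

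- that response can stand for remission, when the 60% is a general background figure and not a planning assumption for this trial;
- that early non-responders never enter the risk set, when follow-up runs to 24 months and the Background says most patients regain normal functioning within three years;
- that the 33% is a rate among remitters, which only the cited trials could settle.

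The at-risk fraction could be higher or lower than 60%. If the rates describe everyone randomised, only the 69–72% applies.

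Two further inferences should not be drawn. The absence of an allowance for loss to follow-up is no finding, because an article may leave it to the full protocol. That the 75 came from a one-sided formula labelled two-sided is plausible, but it is a guess.

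Finally, the named primary outcome is BDI-II severity, not relapse. That limits the consequence, but the relapse calculation is still the stated basis for the size of both active arms.

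**Conclusion.** The concern holds. With CT at 33%, IPT at a derived 53%, proportional hazards and a two-sided 5% test, 75 per arm delivers about 69–72% power, not 80%. The shortfall is 8 to 11 percentage points, or about 16 to 22 at-risk patients per arm (91 − 75 and 97 − 75).

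Separately, the calculation counts all randomised patients for an event that only remitted or recovered patients can have. How much more power this costs depends on the at-risk fraction and on the population behind the 33%, neither of which the article gives. It should therefore be reported as a range, from no further loss down to 48–51% at a 60% at-risk fraction, and not as a single figure.

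**What to change.** Rewrite the first paragraph of Sample size so that it states:

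1. the assumed two-year relapse/recurrence rate in each arm;
2. the population those rates describe (all randomised, or remitted/recovered patients);
3. the assumed fraction of each arm that enters the risk set;
4. in place of the claim that 75 suffices at 80% power, either the power delivered (about 70% for 33% vs 53% if all 75 are at risk, with the lower range above for smaller fractions) or the detectable difference (about 22–23 points with 75 at risk, about 28–30 with 45).

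If the authors used other rates or a one-sided test, they should say so and bring the paragraph into line with the Hypotheses section and the stated two-sided test.

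The change is to the wording of one paragraph. Enrolment, arms, assessments and analyses stay as they are. The only cost is a less favourable stated figure.
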